## Abstract

**Background:**

Although good progress has been achieved in expanding immunization of children in China, disparities exist across different provinces. Information gaps both from the service supply and demand sides hinder timely vaccination of children in rural areas. The rapid development of mobile health technology (mHealth) provides unprecedented opportunities for improving health services and reaching underserved populations. However, there is a lack of literature that rigorously evaluates the impact of mHealth interventions on immunization coverage as well as the usability and feasibility of smart phone applications (apps). This study aims to assess the effectiveness of a smart phone-based app (Expanded Program on Immunization app, or EPI app) on improving the coverage of children’s immunization.

**Methods/Design:**

This cluster randomized trial will take place in Xuanhan County, Sichuan Province, China. Functionalities of the app include the following: to make appointments automatically, record and update children’s immunization information, generate a list of children who missed their vaccination appointments, and send health education information to village doctors. After pairing, 36 villages will be randomly allocated to the intervention arm (n = 18) and control arm (n = 18). The village doctors in the intervention arm will use the app while the village doctors in the control arm will record and manage immunization in the usual way in their catchment areas. A household survey will be used at baseline and at endline (8 months of implementation). The primary outcome is full-dose coverage and the secondary outcome is immunization coverage of the five vaccines that are included in the national Expanded Program on Immunization program as well as Hib vaccine, Rotavirus vaccine and Pneumococcal conjugate vaccine. Multidimensional evaluation of the app will also be conducted to assess usability and feasibility.

**Discussion:**

This study is the first to evaluate the effectiveness of a smart phone app for child immunization in rural China. This study will contribute to the knowledge about the usability and feasibility of a smart phone app for managing immunization in rural China and to similar populations in different settings.

**Trial registration:**

Chinese Clinical Trials Registry (ChiCTR):
ChiCTR-TRC-13003960

## Background

Substantial gains in child survival over the past two decades have been achieved, but still key work is required within the context of the Millennium Development Goals (MDGs) on child survival
[1]. Full-dose coverage of immunization is one of the essential child health strategies and a critical public health objective, which was included in the World Health Organization (WHO)/The United Nations Children’s Fund (UNICEF) Regional Child Survival Strategy as one of the major components of the child survival intervention package
[2]. It is recognized that timely vaccination, particularly within the first six months of life, is extremely important in reducing the burden of disease preventable by vaccines
[3]. WHO stated in 2013 that the estimated number of all deaths of children aged less than 5 years from vaccine-preventable diseases was 1.49 million
[4].

In China, good progress has been made in introducing Bacillus Chalmette Guerin (BCG), Oral Poliomyelitis Vaccine (OPV), Diphtheria Pertussis Tetanus Combined Vaccine (DTP) and Measles Vaccine since the mid-1970s. In 1992, Hepatitis B Vaccine (HBV) was included into the national immunization program. According to the guideline issued by Ministry of Health in China, caregivers of children should go to the local eligible hospitals to register for an immunization card within one month after children’s birth. In rural areas, caregivers usually go to township hospitals or village clinics for immunization services. The township doctors record the name, birth date and other basic information of the children on their immunization cards and inject the age-appropriate vaccines according to the guideline (Additional file
1: Table S1). After that, doctors record the date for the next vaccines and make appointments with caregivers.

The implementation of Expanded Program on Immunization (EPI) has improved the national immunization coverage significantly. According to the fourth National Health Service Survey (NHSS) in 2008, around 80% of Chinese children aged 12–59 months were fully immunized (one dose of BCG and measles, three doses of DPT, HBV and OPV)
[5]. However, it varied greatly among provinces, with the highest in Zhejiang (89.9%), the lowest in Chongqing (46.4%), and a rate in between these two provinces in Sichuan (70.0%). Compared to the national target set for the year 2020 (more than 95% of children fully immunized)
[6], there is a big gap that needs to be closed, especially for areas that have the lowest coverage. A study in Sichuan Province aiming to evaluate the current status of the childhood immunization concluded that the proportion of missed and unqualified vaccination was higher in remote rural areas
[7].

An information gap both from the service supply and demand side hinders timely vaccination of children. A study focusing on the low coverage of full dose immunization found the following reasons for failure of vaccinating children on time: 1) village doctors reported that the time interval between the two injections was too long for them to remember the exact date for next injection, which resulted in the missed or overdue vaccinations. 2) caregivers reported that they did not know where to get vaccination or which doctor was responsible for their children’s vaccination and that they did not inform them of the date for next immunization
[8].

Mobile health (mHealth) may have great potential to address some of the issues and challenges related to the disparity of immunization coverage in rural China. mHealth lacks a unified definition, but can be described as supporting the practice of medicine and public health by mobile devices
[9]. Though the mHealth field is still in its infancy, it can have considerable impact health outcomes by, among other methods,extending the reach of health information and services to remote populations and promoting health services
[9].

Recently, smart phones have found their ways into our lives. They combine the functions of a mobile phone and PDA (Portable Digital Assistant), in addition to enabling Internet access and imaging and video functionality. Apps as an indispensable part of mHealth have obtained more and more attention. Carter et al. showed that an app was acceptable and feasible as an intervention for weight loss
[10]. Whittaker et al. found a multimedia mobile phone smoking cessation program (app) was technically feasible to help the target population to quit smoking
[11]. Both of these studies showed that the apps were acceptable and feasible as health interventions. However, there is a lack of literature that rigorously evaluates the impact of mHealth interventions
[9,12] on childhood immunization coverage
[13,14].

To improve the current status of immunization coverage in rural Sichuan Province, EPI app, a smart phone app, has been developed by Save the Children and will be implemented in two townships of Xuanhan County, Sichuan Province. The aims of this study are to evaluate the usability and feasibility of the app and to explore the effectiveness of a smart phone app on improving immunization of children in rural Sichuan Province, China.

## Methods/Design

### Design

This cluster randomized controlled trial (C-RCT) will evaluate the effectiveness of a smart phone app, the EPI app, on increasing immunization coverage of children in rural Sichuan Province (Figure 
1). The village doctors will use the app to document and manage the vaccination injection records. In some villages, more than one village doctor is eligible for child vaccination and potential contamination will be introduced if we randomize at individual level (for example when a village doctor in the intervention group shares the app with another village doctor in the control group in one village). Therefore, a cluster design will be used and the unit of randomisation and analysis will be the village. The effectiveness of immunization coverage will be collected from a Maternal, Newborn and Child Health Household survey and assessed by comparing outcomes between baseline and endline (8 months after baseline).

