### Sample size and study population

A. Sample size calculation

Base on a survey conducted in early 2013 in Xuanhan County, Sichuang Province, the coverage of the five key vaccines is 41.35%. We expect that the five-vaccination coverage in intervention group will rise from 41.35% to 65%.With level of confidence of 95%, power of 80%, the coefficient of variation in outcome between clusters within matched pairs (Km) as 0.25
[18], we estimate that 7 participants from each cluster of 18 pairs of clusters will be sufficient to detect the difference in two groups.

B. Intervention target will be village doctor in charge of immunization

Inclusion criteria

a. Village doctors who are in charge of immunization (both management and injection)

b. If there are several village doctors available, we will choose the youngest one and with the assistant practicing license for clinical doctors

Exclusion criteria

a. Refuse to participate

b. The estimated number of children aged one to two years in village is less than 7. The estimated number is calculated as the number of children reported multiplied by 75% (the average percentage of children staying in the village) and 90% (the expected rate of contacted primary caregivers who agree and complete the survey).

C. The survey target will be caregivers of children aged 12–23 months. Children aged over 1 year are supposed to complete the five vaccinations required by national EPI program. Therefore, caregivers of children aged 12–23 month old are our survey target in both the baseline and endline survey.

Inclusion criteria

a. Living in Xuanhan County

b. Receiving immunization service in Xuanhan County

c. Having a child aged 12 to 23 months; if there is more than one child aged 12 to 23 months, only include the youngest one

d. Being a caregiver of the selected child

Exclusion criteria

a. Refuse to participate.

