### Data management and analysis

The primary investigator will be in charge of the database maintenance and management. Data will be stored in a computer with passwords. The primary investigator will be responsible for the integrity and accuracy of the data. All participants will have a unique code. Smart phones will be used to collect data. Data will be secured first, then exported and uploaded to the internet into a database. Logic verification statements will be written in data acquisition software for the mobile phone. Statistical analyses will be performed by research staff blinded to the treatment allocation.

The principle of intention-to-treat-analysis will be used. At village level, the five-vaccine immunization coverage or other immunization coverage indicators will be transformed first and compared with paired t test or non-parametric test. Random-effect logistic regression will be used to test for the effect on every outcome when controlled for the covariate (socioeconomic variables such as education level, ethnicity, gravidity, parity, type of Hukou, source of family income) on individual level.

Exploratory statistical analysis of multidimensional evaluation of app will be used to calculate the frequencies and mean severity rating scores of heuristic violations, mean logging time, number of error for each task, score of perceived ease of use and usefulness, the percentage of compliance and frequency of technical or hardware problems. Qualitative materials of the multidimensional evaluation of app will be collected through recordings and evaluation forms. The recording will be transcribed verbatim and compared to field notes for any inconsistency or missing information. Content analysis will be used to analyze qualitative data.

All quantitative analysis will be performed by SAS 9.1 and qualitative analysis will be performed with MaxQDA. P < 0.05 will be considered statistically significant.

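### The protocol describes the effectiveness assessment as baseline against endline but sizes the trial as a single-time-point difference between matched arms; the primary contrast should be fixed, with baseline village coverage used as a covariate

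*Protocol article*

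**What the plan says.** Three sections of the protocol article bear on the primary contrast.

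- **Design:** effectiveness is to be "assessed by comparing outcomes between baseline and endline (8 months after baseline"). The sentence names two time points and no arms. The same paragraph says that "the unit of randomisation and analysis will be the village".
- **Sample size and study population:** the planning assumption is that "coverage in intervention group will rise from 41.35% to 65" per cent. The other inputs are "With level of confidence of 95%, power of 80" per cent, and "the coefficient of variation in outcome between clusters within matched pairs (Km) as 0.25". The conclusion is that "7 participants from each cluster of 18 pairs of clusters will be sufficient to detect the difference in two groups". On who is surveyed: "caregivers of children aged 12–23 month old are our survey target in both the baseline and endline survey".
- **Data management and analysis:** village-level coverage "will be transformed first and compared with paired t test or non-parametric test". Neither the time point nor the use of change is stated. The random-effect logistic regression adjusts for individual socioeconomic variables; baseline coverage of the village is not among those listed.

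The Randomization section places randomisation after the baseline household survey. It matches villages on the number of infants managed, the age of the youngest doctor and population density, and not on baseline coverage.

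**The concern.** The only sentence on how effectiveness will be judged describes a comparison over time, while the sample size rests on a comparison between arms. The test that should link the two leaves its outcome variable open. An analyst could use endline coverage or baseline-to-endline change and cite the protocol for either.

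The two are not interchangeable. A change score carries the sampling error of two small surveys per village, and the sample size allows for one. Leaving the choice open also allows it to be made after the results are seen. In addition, the baseline measurement most relevant to the outcome is available for every village before allocation, yet the stated analysis gives it no role as a covariate.

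**Working it through.** **Inputs.** From the sample size section: p0 = 0.4135, p1 = 0.65 (difference d = 0.2365), km = 0.25, n = 7 children per village, 18 pairs, 80% power. Assumed: two-sided 5% (sidedness is not stated); the correlation r between a village's true coverage at baseline and at endline (not given, so shown from 0 to 1); baseline coverage of 41.35% in both arms; independent samples of children at the two surveys; untransformed proportions.

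**1. Reproducing the stated size.** The matched-pair formula for two proportions at one time point is

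pairs = 2 + (1.96 + 0.84)² × V / d², with V = [p0(1−p0) + p1(1−p1)]/n + km²(p0² + p1²).

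- n = 7: V = (0.2425 + 0.2275)/7 + 0.0625 × (0.1710 + 0.4225) = 0.0671 + 0.0371 = 0.1042. Pairs = 2 + 7.849 × 0.1042/0.0559 = 16.6, within 18.
- n = 6: V = 0.1154, pairs = 18.2, above 18.

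So 7 per village with 18 pairs is what this formula gives, and it has no baseline term. Power at n = 7: the noncentrality is 0.2365/√(0.1042/18) = 3.11, which on 17 df gives **83%**.

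**2. Between-arm difference in change, 7 children per survey.** Baseline adds sampling variance 2p0(1−p0)/7 = 0.0693 and between-village variance 2km²p0² = 0.0214. Village persistence removes 2r·km²(p0² + p0p1) = 0.0550r. Hence V = 0.1042 + 0.0693 + 0.0214 − 0.0550r.

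| r | V | Power |
|---|---|---|
| 0 | 0.195 | 57% |
| 0.5 | 0.167 | 64% |
| 0.8 | 0.151 | 68% |
| 1 | 0.140 | 72% |

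By the formula in step 1, this contrast needs 22 to 30 pairs at 7 per village, or 9 to 18 children per village with 18 pairs.

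**3. More children per village.** With 12 per village at each survey, change-score power is 72% (r = 0) to 91% (r = 1); with 15 it is 77% to 95%.

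**4. Some children surveyed twice.** Children aged 12–15 months at baseline are 20–23 months at endline, so up to 4 of the 12 monthly age groups could recur. As an extreme bound, suppose one third of the 7 recur and no vaccinated child loses that status. V then falls by 2 × (0.2425 + 0.4135 × 0.35)/21 = 0.037. Change-score power becomes 66% (r = 0) to 84% (r = 1), reaching 80% at r = 0.8. The actual overlap cannot be derived from the document.

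**5. Endline adjusted for baseline village coverage.** The residual variance is 0.1042 × (1 − ρ²). Here ρ is the correlation between observed baseline and endline within-pair differences, r × 0.0275/√(0.1042 × 0.0907), which runs from 0 to 0.28. V is 0.104 to 0.096 and power **83% to 86%**, with the same rounded values on 16 df, after the covariate's degree of freedom is spent.

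**The case against.** The strongest defence is that the trial plainly compares arms. The article calls itself a cluster randomised controlled trial, allocates villages to intervention or control, and specifies intention-to-treat and analysts blinded to allocation. It uses pairing only for matched villages: one village is dropped to keep the pairs even, and km is defined within matched pairs. The paired t test is then most naturally a test across the 18 village pairs, and the Design sentence is loose wording. This stands. A reader might infer from the Design sentence that a before-after test in the intervention villages is planned, so that any secular rise in coverage would be credited to the app. The document does not support that: it specifies no single-arm test and gives no figure for a secular trend.

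The second defence is that 7 per village is a minimum. It is described as sufficient and also serves as the exclusion threshold for small villages; no cap is stated. The Study area section gives 1,350 + 560 = 1,910 children under 2 in 31 + 15 = 46 villages. If half are aged 12–23 months, the protocol's own 75% and 90% factors leave 1,910/2/46 × 0.75 × 0.90 ≈ 14 per village on average. This also stands, and it makes the power loss conditional.

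Third, randomisation already makes an unadjusted endline comparison valid. That is right, and it would be wrong to infer that omitting baseline coverage biases the result. A change score would itself use baseline, so the absence of adjustment concerns only an endline test and the regression.

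Finally, an analysis plan might settle the contrast. It would still have to depart from either the Design sentence or the basis of the sample size, which already differ within the protocol.

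**Conclusion.** The point holds as a should-fix inconsistency. The Design, sample size and analysis sections do not agree on one primary contrast: the sizing supports a between-arm difference at endline (about 83% power), and the Design wording fits at best a difference in change. Under the latter, power is 57–72%, below the stated 80%, if 7 children per village are surveyed each time and the two samples are independent. Larger village samples or repeated children would narrow or remove the shortfall, and neither can be settled from the document. Using the baseline coverage already collected is a gain in precision of 0 to about 3 percentage points of power at 7 per village. It does not correct an invalid analysis.

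**What to change.** - In the Design and the Data management and analysis sections, state the primary contrast as the within-pair intervention-minus-control difference in endline village coverage, adjusted for baseline village coverage.
- State that the pairs in the village-level test are the matched villages.
- Add baseline village coverage to the random-effect logistic model.
- Report baseline-to-endline change by arm descriptively, and reword the Design sentence to match.

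The cost is a few sentences and one degree of freedom in the village-level analysis. No new data are needed, and the stated sample size stays consistent with the primary test.

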**Figure 1 F1:**
[figure not shown]
Flowchart of study.

The EPI app was developed by Save the Children and managed jointly by Save the Children and Xuanhan Centers of Disease Control and Prevention (CDC). Capital Institute of Pediatrics will be involved in the monitoring and evaluation process. Villages will be randomly allocated to one of two groups: the intervention group where the village doctors use a smart phone with EPI app to record and manage the vaccination and the control group where the village doctors use usual way to record and manage the vaccination (Figure 
2).

**Figure 2 F2:**
[figure not shown]
Management of immunization of children at township and village level.

### Study area

This trial will be conducted in Nanba and Xiaba Township, Xuanhan County in Dazhou City, Sichuan Province, China. Sichuan Province is located in the west part of China with an area of 486,000 km^2^ and has 21 cities and 183 counties. By the end of 2012, the total population in Sichuan Province was 80,762,000. In 2012, the annual per capita net income of rural residents was 7,001 Yuan
[15]. Xuanhan County covers an area of 4,271 km^2^ and has a total population of 1,170,000. It has 55 townships and 497 villages
[16]. Nanba Township has 31 villages with a total population of 100,000 and under 2 population of 1,350; Xiaba Township has 15 villages with a total population of 33,750 and under 2 population of 560.

### Intervention

#### Development of the EPI app

The Android-based EPI app was developed specifically for Xuanhan County, Sichuan Province, China by an information technology company (Cybermax, 金卫信). A smart phone app was chosen over other information communication technology solutions for the following reasons: 3G wireless networks have better coverage than broadband networks, the cost of smart phone is lower than a computer or laptop and it is easier to carry a smart phone when village doctors conduct out-reach services. The development process started with a needs assessment of village doctors in December 2012. After reaching consensus with Save the Children, a study supervision team consisting of different stakeholders including project partner PATH, local health authorities, CDCs, township hospital health workers and village doctors, and the app developer, a requirement specification of the EPI app was made early 2013. The first version of EPI app came out in September 2013 and further pilot testing and revising the app was conducted between September 2013 and March 2014.

#### Training village doctors to use EPI app and subsequent support

In January 2014, intervention village doctor each took part in a one-day training workshop on the use of EPI app. The trainers, who are the developers of the EPI app, used a variety of techniques, including interactive lectures, demonstrations and skills practice. To be judged as competent, each village doctor had to complete a skills assessment test satisfactorily.

Refresher workshops have been planned twice afterwards throughout the study. Village doctors are compensated for their travel costs and food while attending the workshops. None of the participants receive salary support or other incentives for their participation in the study. After the initial training, each village doctor in the intervention arm is provided with a 3G wireless network smart phone with the pre-installed EPI app. All the fees including phone calls, text messaging and internet access will be paid by the program. If village doctors encounter any problems when using the app during the study, they can call the township doctors for help, or if not solved by township doctors, technical support from the developer team will be provided. Moreover, a technician from the app development company will stay in our study area after the initial training to provide immediate technical support.

